#### Analysis plan

Analysis of the primary objective will be completed when every patient has completed all of the diagnostic tests. All statistical testing will be performed at a 2-sided 5% significance level. A final statistical analysis plan will be written and reviewed before any statistical analysis is undertaken.

#### Analysis populations

The analysis population for the primary objective will include all patients who have results for both CMR and X-ray angiography. The analysis populations for the secondary objectives will include all patients who have the appropriate data for each comparison. Patients withdrawing from three year follow-up will be censored at the time of withdrawal.

#### Missing data

The numbers of patients with missing data for one or more tests, and the numbers of uninterpretable tests will be reported. Patients with missing data for one or more diagnostic tests will be excluded from any comparisons involving those tests.

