### Statistical considerations

#### Sample size

For our primary objective, estimating the diagnostic accuracy of CMR against the reference standard of X-ray angiography we calculated that a sample size of 750 patients would enable us to estimate the sensitivity or specificity of CMR to within +/-3.5%. This assumes a sensitivity (or specificity) of 90% for CMR and 60% prevalence of significant CHD in the study population and is based on the precision of the 95% confidence interval for a proportion. For the secondary objectives of comparing the diagnostic accuracy of CMR with SPECT and also ETT, this number would be sufficient to detect a 6.5% difference in sensitivities (or specificities) between CMR and SPECT with 80% power, assuming a sensitivity of 85% for SPECT and 2-sided analyses at the 5% significance level [22]. As the sensitivity and specificity of ETT is expected to be lower at around 68% sensitivity and 77% specificity, our sample size will provide sufficient power to detect the expected larger differences between CMR and ETT.

To assess the prognostic value of CMR in predicting MACE approximately 10 events are required for each prognostic factor in the statistical model [23]. The prognostic value of the combined CMR conclusion will be assessed after adjusting for the known risk factors age, gender, cholesterol, blood pressure, smoking and diabetes, which would require 70 events. It is estimated that approximately 30% of patients will undergo planned revascularisation based on the angiogram result and for this to be carried out usually within 8 weeks. For the remaining patients we estimate that for every 70 patients, 10 will be normal with an event rate of <1% per year and 60 will have CHD (30 significant and 30 mild) with an event rate of approximately 5% per year. The required sample size of 750 patients for the diagnostic accuracy evaluation would therefore result in approximately 23 patients experiencing an event per year. With a minimum follow-up period of 3 years this would provide the required number of 70 patients with an event.

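### Accuracy is planned only among patients whose tests gave a result; failed CMR and SPECT scans have no stated role in the estimates or the paired comparison

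*Protocol article*

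**What the plan says.** The protocol article states a rule on this point.

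- **Analysis populations:** the primary analysis is to "include all patients who have results for both CMR and X-ray angiography". Populations for the secondary objectives are defined comparison by comparison, according to which data are available.
- **Missing data:** "Patients with missing data for one or more diagnostic tests will be excluded from any comparisons involving those tests". The same section promises counts of patients with missing tests and of uninterpretable tests. It does not say whether an uninterpretable test is treated as missing, positive or negative.
- **Test conduct:** the number of patients having each test is to be reported, with reasons for non-performance where known.
- **Comparison of CMR with SPECT and ETT:** sensitivities and specificities are compared by McNemar's test, which needs both results from each patient.
- **Sample size:** "a sample size of 750 patients would enable us to estimate the sensitivity or specificity of CMR to within +/-3.5" percent. "This assumes a sensitivity (or specificity) of 90% for CMR and 60% prevalence of significant CHD in the study population".

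The article names no sensitivity analysis for failed tests.

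**The concern.** The Background presents CMR as a way to decide which referred patients need invasive angiography. For that purpose a scan that gives no answer is part of the test's performance, because the patient still needs another investigation. The Background already reasons this way about exercise testing, where it lists inability to complete an adequate test among the limitations. It also criticises earlier CMR and SPECT studies for selection bias, and restricting the analysis to patients with results adds a selection step of its own.

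Some failures are plausible. The CMR examination takes about an hour and includes adenosine stress, repeated breath-holds and a navigator-gated coronary acquisition. Image quality is graded, but no rule is given for a study that cannot be read.

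Two results are at stake. The headline accuracy describes patients with a successful scan and could be read as describing all referred patients. In the comparison with SPECT, a failure of either test removes the pair, so a test that fails more often bears no penalty.

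**Working it through.** **Inputs from the article (Sample size).** 750 patients; 60% prevalence, so 450 with and 300 without significant CHD; 90% sensitivity or specificity for CMR; 85% sensitivity for SPECT; a target difference of 6.5 points. No CMR or SPECT failure rate is given, so every failure rate below is an assumption.

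**1. The plan's own figure.** The stated precision "is based on the precision of the 95% confidence interval for a proportion". The half-width is 1.96 × √(0.9 × 0.1 / n):

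- sensitivity, n = 450: 2.77 points
- specificity, n = 300: 3.39 points

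Both lie within 3.5 points, so the figure is reproduced.

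**2. Does losing patients harm precision?** Hardly. With 5% lost, 285 patients without CHD remain and the specificity half-width is 3.48 points. With 10% lost, 270 remain and it is 3.58 points. The issue is what the estimate means, not the sample size.

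**3. Failures counted as positive.** Let u be the share of attempted scans that fail, taken as equal in patients with and without CHD. Then specificity = 0.90 × (1 − u) and sensitivity = 0.90 × (1 − u) + u.

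| u | Specificity | Change (points) | Sensitivity | Change (points) |
|---|---|---|---|---|
| 3% | 87.3% | −2.7 | 90.3% | +0.3 |
| 5% | 85.5% | −4.5 | 90.5% | +0.5 |
| 8% | 82.8% | −7.2 | 90.8% | +0.8 |

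The specificity loss is 90 × u points. It passes 3.5 points when u exceeds 3.5 / 90 = 3.9%.

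**4. Failures counted as wrong (worst case).** Sensitivity and specificity both become 0.90 × (1 − u): 88.2% at 2%, 85.5% at 5% and 81.0% at 10%.

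**5. Direction.** Suppose the failed scans would have been read with accuracy a. The available-case figure then exceeds accuracy over all attempted scans by u × (0.90 − a). At u = 5% this is +4.5 points for a = 0, +2.0 for a = 0.5, zero for a = 0.9 and −0.5 for a = 1. The sign is not fixed.

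**6. CMR minus SPECT sensitivity, failures counted as wrong.** The difference is 90 × (1 − CMR failure rate) − 85 × (1 − SPECT failure rate), in points. With no failures it is 90 − 85 = +5.0.

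| CMR failures | SPECT failures | Difference (points) |
|---|---|---|
| 5% | 2% | 85.5 − 83.3 = +2.2 |
| 10% | 2% | 81.0 − 83.3 = −2.3 |
| 2% | 5% | 88.2 − 80.75 = +7.45 |
| 2% | 10% | 88.2 − 76.5 = +11.7 |

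The shifts from +5.0 are −2.8, −7.3, +2.45 and +6.7 points. At the larger assumed rates they exceed the 6.5-point difference that the study is sized to detect.

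**The case against.** The strongest defence is that analysing patients with both results is a legitimate primary choice for an objective framed as accuracy against angiography. Failures are not hidden either, since counts and reasons will be published. Eligibility removes several causes of failure by requiring sinus rhythm and a weight below 110 kg and by excluding patients who cannot lie supine for an hour. The primary analysis also uses a combined CMR conclusion, so one poor component need not leave the patient without a result. Finally, the article promises a statistical analysis plan, which could add a sensitivity analysis.

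Much of this stands, and it lowers the likely failure rate. But published counts do not enter the estimates or McNemar's test, and the article itself fixes the populations and the exclusion rule that a later plan would inherit.

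A reader might also infer more than the text supports:

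- **That a patient with any failed test leaves every accuracy estimate.** Exclusion is test by test. A patient lacking only SPECT or ETT stays in the primary CMR analysis.
- **That uninterpretable scans are expressly excluded.** The exclusion sentence names missing data only. Exclusion of unreadable scans is inferred from the requirement for a result.
- **That the rule inflates CMR accuracy.** This is not shown. The direction depends on the failed scans, and counting them as positive raises sensitivity slightly.
- **That the rule favours CMR over SPECT.** If SPECT fails more often, the rule works against CMR.

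**Conclusion.** The point holds as a limitation of what the planned estimates describe, and one that is cheap to remedy. Under the stated rule, a CMR or SPECT test without a result cannot affect that test's sensitivity or specificity, or the paired comparison. The figures are conditional on a successful test and may overstate performance in referred patients, chiefly specificity if failed scans lead to angiography.

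The size rests wholly on assumed failure rates, on 90% accuracy in readable scans, and on equal failure in patients with and without CHD. For 3% to 8% failures counted as positive, specificity falls by 2.7 to 7.2 points and sensitivity rises by 0.3 to 0.8 points. The effect on the CMR–SPECT difference could go either way.

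**What to change.** In Analysis populations and Missing data, keep the available-case analysis and add:

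- a statement of how an uninterpretable or aborted test is classified;
- a pre-specified intention-to-diagnose sensitivity analysis, shown beside the available-case result. It would include every patient with an angiography result in whom the test was attempted, and count a failed CMR or SPECT as test-positive;
- a worst-case version in which failures are counted as wrong;
- the CMR versus SPECT McNemar comparison repeated on this same set;
- exclusion from this analysis only of tests never attempted for reasons unrelated to the test.

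The counting rule is an analysis convention and says nothing about patient management. The change needs no new patients or data. It costs a few lines of text, a little extra analysis and possibly a less favourable specificity.

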#### Test conduct

The numbers of patients undergoing each test will be reported along with reasons why the test was not performed, where available. The duration between the CMR and X-ray angiography and also between the SPECT and X-ray angiography will be summarised. Details of the order of the testing sequences for each patient will also be summarised.

### Primary objective

#### Diagnostic accuracy – CMR compared to angiography

The sensitivity, specificity, positive and negative predictive values and corresponding 95% confidence intervals for the diagnostic performance of CMR in detecting the presence of significant CHD as confirmed by the X-ray angiogram will be calculated. This will evaluate the combined CMR conclusion. Additional analyses will also be performed to explore the diagnostic accuracy of the individual CMR components: late enhancement, perfusion, contractile function and CMR coronary angiography. These components will be examined alone and in combination (with a positive result for CHD on one or more tests being taken as a positive overall) to identify which component of the CMR data has the best ability to detect CHD.

### Secondary objectives

#### Comparison of CMR with SPECT and ETT

The sensitivity, specificity, positive and negative predictive values and corresponding 95% confidence intervals for the diagnostic performance of SPECT and ETT compared with the X-ray angiogram will be calculated. For the comparison of CMR with SPECT and also with ETT we will use McNemar's test to compare the sensitivities and specificities.

#### Prognostic value of CMR (at 3 year follow-up)

The prognostic ability of the combined CMR result alone and after adjusting for the risk factors: age, gender, cholesterol, blood pressure, smoking and diabetes in predicting time to the first major cardiovascular event will be assessed using Cox proportional hazards modelling. Patients not experiencing an event will be treated as censored at their last known follow-up assessment. Hazard ratios and 95% CI will be reported and Kaplan-Meier curves will be calculated. This analysis will be for all patients. Allowing physicians access to SPECT results is ethically unavoidable but may also influence revascularisation decisions and thus introduce an analysis bias. In order to account for any possible bias and any differences in the risk of future events resulting from decisions about revascularization we will conduct additional analyses which will adjust for the impact of revascularization on outcomes by treating it as an intermediate event, using time-dependent covariates and multistate models[24].

#### Adverse events

All serious adverse events that occur as a result of the diagnostic tests will be reported by diagnostic test. No formal statistical testing will be undertaken.

#### Cost effectiveness

The cost-effectiveness of alternative diagnostic strategies will be evaluated using data from CEMARC and published sources. This will take the form of a decision analytic model, which will provide a framework to link CEMARC data on the diagnostic accuracy of the alternative forms of diagnosis, information on therapeutic implications and evidence on the ultimate costs to the UK National Health Service and health benefits to patients in the form of quality-adjusted life-years (QALYs) [25]. In addition to information on diagnostic accuracy, CEMARC will provide data on clinicians' therapeutic plans following diagnostic information provided by the alternative diagnostic modalities. CEMARC will also provide data on the costs of diagnostic tests. Using evidence from relevant systematic reviews, the effects and costs of those therapies for a given type of patient will be estimated and incorporated into the model. The cost-effectiveness of alternative diagnostic strategies will, therefore, be determined by the extent to which the information they provide results into cost-effective changes in treatments. Modelling methods to reflect long-term implications of changes in therapy for QALYs and costs will reflect recent models published in the cardiovascular area [26-28]

The general methods used will follow those defined as good practice by the National Institute for Health and Clinical Excellence (NICE) [29]. This will include modelling the full range of diagnostic strategies which would be considered in the National Health Service (NHS), using systematically identified estimates for all input parameters, the use of probabilistic sensitivity analysis to express the uncertainty in all elements of evidence in terms of the probability that each diagnostic strategy is the most cost-effectiveness and further scenario analysis to explore the implications of key assumptions made in the model. We will also use value of information analysis to assess where future research in this area is likely to be the most valuable [25].

### Data monitoring

Data will be monitored for completeness and quality by the CTRU. A full monitoring schedule, including Serious Adverse Events and Adverse Reactions, will be established and agreed by the Programme Steering Committee (PSC) and Study Management Group (SMG).

## Discussion

The CE-MARC study is a prospective, diagnostic accuracy cohort study in a population of 750 out-patients presenting with chest pain. It aims to assess the diagnostic accuracy, for detection of significant CHD, using a multi-parametric CMR protocol versus X-ray coronary angiography, nuclear scintigraphy (SPECT) and exercise tolerance testing (where feasible). The prognostic value of CMR and its cost effectiveness will also be compared with these modalities. CE-MARC will be the largest prospective trial to date to compare CMR against standard non-invasive investigations for the diagnosis of CHD, and may have important implications for the wider adoption of CMR in the future.
